##### Objective 2.3: Potential Interaction of Socioeconomic Status With the Intervention Effectiveness

As mentioned in the previous sections, the role of socioeconomic status will be explored in objectives 1.1.a, 1.1.b, 2.1, and 2.2 by conducting group-specific analyses for the low, moderate, and high socioeconomic groups (refer to the above-mentioned sections for further details).

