2.2. The identification of potential spillover effects and covariations among different food groups (eg, meat, fruits and vegetables, and ultraprocessed food) and dietary outcomes (ie, diet composition and food waste) occurring over the study

2.3. The identification of potential interaction effects between socioeconomic status and intervention effects on behaviors

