### Data Analyses

#### Sample Size and Power Analyses for the Quantitative Side of the Project

The sample size for this pilot study is constrained by financial and human resources. We plan to recruit a total of 21 participants, with 7 participants in each subjective socioeconomic group (refer to the *Participants* section). However, in terms of statistical power, we will benefit from the intensive longitudinal nature of the study, that is, 15 evaluation weeks and up to 105 daily observations per participant. For objective 1.1.a, for which a weekly environmentally sustainable healthy diet index will be used, up to 315 observations will be available in total (21 participants × 15 evaluation weeks) and 105 observations per socioeconomic group (7 participants × 15 evaluation weeks). For objective 1.1.b, for which the daily raw data will be used, up to 2205 observations will be available in total (21 participants × 105 daily assessments), 735 observations in the 3 socioeconomic groups (7 participants × 105 daily assessments), and 105 observations at the individual level (as a general rule of thumb, a minimum of 70 observations are required for conducting individual-level analyses [48]). Given the pilot nature of this trial, we conducted power simulation analyses only for objective 1.1.a (ie, change in the weekly level of food healthiness and environmental sustainability). Considering group-level analyses and the analytical strategy detailed in the next section and assuming an increase of 2 units in the environmentally sustainable healthy diet score per phase, simulated power analysis indicated an adequate power value of 96%. The simulation was performed by generating the response variable as follows:

Fixed effects: the intercept was set at 6, and the fixed coefficient for the phase was set as −2 for the initial phase and +2 for the final phase based on our average expected change in the main outcome.Random effects: it was assumed that each participant would have both a random slope and a random intercept and that both followed normal distributions, with SDs of 2 for the intercept and 0.5 for the slope. The correlation between them was set as 0.2. The random effect for each participant was created by drawing random numbers from a multivariate normal distribution whose covariance matrix was specified using these parameters (R mvrnorm from the package *MASS*).

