##### Objective 1.1.a: Changes in the Environmental Sustainability and Healthiness of Diet

To test the main effect of the intervention on the environmental sustainability and healthiness of diet at the group level, linear mixed regression will be performed and expressed as measurement occasions (here, going from 1, first evaluation week, to 15, last evaluation week), using an ordered 3-categories phase variable as a fixed effect, which takes the values of baseline, intervention, and follow-up. Polynomial functions will also be fitted to the time variable to determine whether the index demonstrates any nonlinear patterns across time. If nonlinear patterns are detected, then other patterns (eg, quadratic, cubic, and piecewise) will be examined and selected based on visual inspections and goodness-of-fit indicators. Moderation analysis will be performed by exploring the role of the subjective socioeconomic level (ie, 3 socioeconomic groups entered as fixed effect) with regard to changes in diet. Fixed baseline characteristics will be included as control variables (ie, age, gender, education, income, and political orientation). Individual trajectories will be plotted, and heterogeneity in participants’ responses to the intervention will be discussed based on visual analyses using relevant guidelines for n-of-1 trials [50] (individual weekly changes in the whole diet will not be statistically modeled because only 15 observations will be available per participant).

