##### Objective 2.1: Identifying Potential Mechanisms of Action Mediating the Effect of the Intervention on Eating Behaviors

Longitudinal mediation analyses will be conducted to understand the processes through which the intervention will potentially affect the environmental sustainability of eating behaviors. These analyses will be conducted independently for the 7 potential mediators presented in the section *Mechanisms of Action* (ie, motives for health, environmental, social, and affordability; ecoanxiety; habits; and self-efficacy) and by following recent guidelines based on longitudinal multilevel structural equation models [51]. These analyses will be performed for the total sample and per socioeconomic subgroup with the environmentally sustainable healthy diet index as the first dependent variable and, in secondary analyses, with the weekly level of the relevant food outcomes mentioned in objective 1.1.b (ie, red and processed meat, fruits and vegetables, ultraprocessed food, dairy products, and food waste). These food groups and food waste will be analyzed here at the weekly level to match the temporal resolution of the mechanisms of action that are also assessed weekly (and not daily).

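### Objective 2.3 asks for a socioeconomic status by intervention interaction, but the stated analyses are separate fits in groups of 7 and a group fixed effect, with no phase-by-group term

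*Protocol article*

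**What the plan says.** The objectives listed at the end of the Introduction (Prior Work) give 2.3 as "The identification of potential interaction effects between socioeconomic status and intervention effects on behaviors". The Data Analyses section for objective 2.3 says the question will be explored within objectives 1.1.a, 1.1.b, 2.1 and 2.2 "by conducting group-specific analyses for the low, moderate, and high socioeconomic groups", and refers back to those sections for detail.

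Objective 1.1.a describes a linear mixed regression "using an ordered 3-categories phase variable as a fixed effect, which takes the values of baseline, intervention, and follow-up". It then adds: "Moderation analysis will be performed by exploring the role of the subjective socioeconomic level (ie, 3 socioeconomic groups entered as fixed effect"), and the sentence goes on to relate this to changes in diet. Objective 1.1.b follows a similar strategy with daily data. For the mediation models of objective 2.1, "These analyses will be performed for the total sample and per socioeconomic subgroup". Objective 2.2 also estimates its networks by subgroup.

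On numbers, the sample size section says "We plan to recruit a total of 21 participants, with 7 participants in each subjective socioeconomic group", giving up to "105 observations per socioeconomic group (7 participants × 15 evaluation weeks"). Power was simulated for objective 1.1.a only.

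**The concern.** An interaction is a difference between groups in the change from baseline to intervention. Three separate analyses give three estimates of change, but neither an estimate of how far they differ nor an interval for that difference. A group fixed effect without a product term answers another question: whether groups differ in average diet score over the year. Neither one responds to the quantity that objective 2.3 names.

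The plan gives this question some weight. The Participants section justifies stratified recruitment by the need to assess differential impact, and the Conclusions say the study will help determine moderation and interaction effects. With 7 people per group, results that differ by chance could be taken for a socioeconomic gradient and carried into the randomized trial that the pilot is meant to inform.

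**Working it through.** **The plan's own figures.** The observation counts reproduce: 21 × 15 = 315, 7 × 15 = 105, 21 × 105 = 2205 and 7 × 105 = 735. The 96% power concerns the phase effect in the whole sample, not the interaction. It cannot be reproduced uniquely because no residual SD is given.

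**Inputs from the plan.** There are 7 participants per group, a random slope SD of 0.5, an assumed effect of 2 index units per phase, a significance level of 0.05, 2 baseline weeks and 15 evaluation weeks in all.

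**Assumptions.** Residual SD s = 1, 1.5 or 2; the slope SD applies to the phase change; 7 intervention weeks (with 6 follow-up weeks, 2 + 7 + 6 = 15); complete data; two-sided tests.

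**Step 1: precision of the change in one group.** A person's intervention mean minus baseline mean has variance 0.5² + s²(1/2 + 1/7) = 0.25 + s² × 9/14. For 7 people, SE = √[(0.25 + s² × 9/14)/7]:
- s = 1: √(0.893/7) = 0.357
- s = 1.5: √(1.696/7) = 0.492
- s = 2: √(2.821/7) = 0.635

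**Step 2: separate analyses when there is no interaction.** Let p be the power in one group (noncentral t, 6 df). The chance that some but not all of the three groups are significant is 1 − p³ − (1 − p)³.

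| s | p, 1-unit change | split result | p, 2-unit change | split result |
|---|---|---|---|---|
| 1 | 0.648 | 68% | 0.996 | 1% |
| 1.5 | 0.401 | 72% | 0.920 | 22% |
| 2 | 0.265 | 58% | 0.747 | 57% |

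The result depends heavily on effect size and noise. At s = 3, where the whole-sample baseline-to-intervention contrast happens to give 96.1% power, the split chances are 38% (1 unit) and 74% (2 units).

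**Step 3: group main effect against interaction.** Three groups of 7 were simulated 4,000 times per setting, at s = 1, 1.5 and 2.
- True changes of 0, 1 and 2 units, equal average levels: the main-effect test rejects about 5% of the time, which is its alpha. A test of group differences in change rejects 91%, 64% and 42%.
- Equal changes, levels differing by −2, 0 and +2: the main-effect test rejects 83–86%, and the test of differences in change about 5%.

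A main effect therefore misses real moderation and picks up differences in level instead.

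**Step 4: what a correct analysis can detect.** The SE of a difference between two groups is the Step 1 SE × √2 = 0.505, 0.696 and 0.898. With 18 df (21 − 3), 80% power needs a difference of about 1.5, 2.1 or 2.7 units. Power for a 1-unit difference is 47%, 28% and 18%.

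**The case against.** The strongest reply is that the objective 1.1.a sentence calls itself a moderation analysis and ties it to changes in diet. On that reading the parenthesis only says that group is a fixed and not a random factor, and a phase-by-group term was meant. The objective 2.3 section refers back to that text. This stands in part: a reader might infer that the authors settled on a main effect only, and the document does not support that as a statement of intent. But the only specification given contains no product term, and the objective 2.3 section names group-specific analyses as the method. This is more than detail left to a fuller document, because a method is stated and it does not yield the quantity asked for.

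A reader might also infer that the plan will compare significance across groups and declare a gradient. It states no such rule; it says the role of socioeconomic status will be explored. The split-result percentages in Step 2 therefore show the hazard of reading separate results side by side. They are not the error rate of a declared test.

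Finally, the objective is secondary, the study is a resource-limited pilot, and the Discussion states no clear hypothesis for 2.3. All of that stands and limits severity.

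**Conclusion.** The point holds on the text: the objective is an interaction, and no stated analysis estimates a between-group difference in change. This conclusion rests on the wording and needs none of the numerical assumptions. The size does need them. With equal true change in all groups, separate analyses would split on significance about 58–72% of the time at 1 unit and about 1–57% at the plan's 2 units, for residual SD 1–2. The 1-unit case is relevant because the Discussion expects only small to medium effects, but it is not the plan's power assumption, so both belong in the account.

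Severity is moderate. The primary phase analysis is untouched, and even a correct interaction analysis would be imprecise. Nor does the point require that subgroup mediation be dropped. Those models have only 7 people each at the person level, although up to 105 weekly observations, and whether to keep them is a separate trade-off.

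**What to change.** In the objective 1.1.a section, and likewise in 1.1.b, specify one full-sample mixed model with phase, group and phase-by-group. With three phases and three groups this adds (3 − 1) × (3 − 1) = 4 interaction terms. Keep the person-level random slope so that group differences are judged against variation between people.

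Report the between-group differences in intervention-minus-baseline change with 95% intervals, labelled exploratory, as the answer to objective 2.3. Because phase is declared as ordered, state this contrast explicitly and do not rely on default coefficients. Cross-refer to it in the objective 2.3 section. Keep group-specific estimates as description only, including subgroup mediation if it is retained.

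The cost is a few sentences and four parameters, in a model that already carries five baseline covariates for 21 participants. No new data are needed. The downside is visibly wide intervals, with only differences of about 1.5–2.7 units detectable at 80% power under the assumptions above.

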#### Qualitative Data Analysis

The qualitative data will be analyzed using framework analysis, a thematic-oriented approach to qualitative data analysis that is gaining popularity in the health sciences and is well suited for analyzing data from semistructured interviews [54,55]. The output of this method is a matrix containing the participants in the rows, analytical codes in the columns, and a data summary in the cells. Using this matrix, researchers can compare the participants’ views within each participant and across participants, thereby identifying patterns across the data set (ie, code-based analysis) while preserving the context of the participants’ views (ie, analysis by case). In addition, because of the structured nature of the method, framework analysis is helpful in studies that involve multidisciplinary research teams with a majority of members having quantitative expertise, such as this study. In this study, framework analysis will be implemented according to the following 6 steps outlined by Gale et al [55]: familiarizing with the interview transcripts, coding the transcripts, developing a working analytical framework by grouping the codes, applying the analytical framework to the transcripts, charting data into the framework matrix, and interpreting the data. Two researchers will independently code and apply the analytical framework. Disagreements between the researchers will be discussed until a consensus is established, if required, with the assistance of a third researcher.

#### Integration of the Quantitative and Qualitative Data

After completing all the analyses, a back-and-forth process will be used to integrate the quantitative and semistructured interview findings [56]. Joint displays will be used to facilitate this process, an increasingly used visual tool designed for facilitating integration in mixed methods studies [57]. Specifically, using joint displays, both quantitative and qualitative findings for objectives 1.1.a, 1.1.b, 1.2, and 2.1 will be juxtaposed, and the extent to which the qualitative results confirm, reject, complement, or expand on the quantitative results will be assessed. By integrating the quantitative and qualitative findings, a more comprehensive and fine-grained understanding of the effectiveness, feasibility, and implementation of the intervention will be gained.

### Ethics Approval

This study was approved by the Drug Research Ethical Committee (CEIm) of Parc de Salut MAR on October 19, 2022 (2022/10304/I), and will be conducted in accordance with the Helsinki Declaration. The participants will be required to provide written informed consent to participate in the study during the baseline visit before any study procedure.

## Results

This study was approved by the Ethics Committee on 19 October, 2022. It started in October 2022. The initial results are expected to be published in May 2023. The final results are expected by October 2023.

## Discussion

### Principal Findings

With regard to objective 1.1.a, we expect environmentally sustainable healthy diet to positively change over time (increasing score for the environmentally sustainable healthy diet index) with small to medium effect sizes, as observed in most previous behavior change interventions [14]. With regard to objective 1.1.b, which focuses on food groups and food waste and reflects the changes in the index, we expect the consumption of meat, dairy products, and ultraprocessed food to decrease over time and the consumption of unprocessed or minimally processed plant-based foods to increase. However, the rate of change might differ from one food group to another; for example, an increase in fruit and vegetable consumption might occur earlier in the intervention than a decrease in meat consumption, which might indicate that this second behavior is more difficult to change. At the individual level, we also expect the shape of those changes to be heterogeneous across participants, with linear improvements, 1-step changes, and inverse U–shape, for example. Objective 1.2 (feasibility of the study) is not hypothesis driven.

With regard to objective 2.1, we expect substantial mediation effects of motivations, ecoanxiety, habit, and self-efficacy on eating behaviors, with positive changes in eating behaviors being partially explained by positive changes in these variables. More specific hypotheses can also be formulated; for example, we expect motivation for protecting the environment to mediate changes in the food groups with the highest environmental impact (eg, meat) more than those in the food groups mainly relevant for health (eg, ultraprocessed food).

We do not have clear and specific hypotheses regarding the covariations among food groups and among dietary outcomes (objective 2.2) and hypotheses regarding the moderating role of participants’ socioeconomic level (objective 2.3), given that only a few studies have examined these dimensions before; overall, the participants from the lowest socioeconomic group may present a less healthy and environmentally sustainable diet than the participants belonging to the higher socioeconomic groups [27,58].

### Limitations

Our primary outcome is a weekly score of environmentally sustainable healthy diet created based on daily food measures to avoid recall bias. This specific questionnaire and scoring procedure have not yet received proper validation. However, this does not constitute a limitation to us. The questionnaire gathered common food groups and framed them as in other digital food frequency questionnaires validated for the Spanish population [59]. It provides information about specific foods gathered in each group with the serving size. The reason for using this customized tool instead of any previously validated is that this study is among the first to monitor changes in environmentally sustainable healthy diet as a whole and through dynamic daily assessments (instead of lower resolution measures, eg, monthly assessment), thus justifying the use of a new and shorter measurement tool. Similarly, the lack of validation of our scoring procedure is not a major limitation given that (1) this study is a pilot study and the data gathered will also be used to refine our scoring procedure later in time and that (2) the score is developed in a straightforward manner based on the EAT-Lancet Commission, and Food and Agriculture Organization, and World Health Organization recommendations [25,40,41]. Our team is conducting parallel validation studies of this questionnaire and scoring procedure, and we also expect to use the data from this pilot intervention to examine the sensitivity of the tool to detect behavior changes (with the ultimate aim of refining this questionnaire and scoring procedure for future interventions).

### Comparison With Prior Work

We prefer performing n-of-1 trials rather than adopting other traditional designs, such as parallel randomized control trials, because the former present some advantages, including (1) the possibility of developing efficient studies (in terms of time and human and financial resources) with few participants involved but providing forms of causal inference to quantify the intervention’s effectiveness for each participant (ie, within-individual randomization and time effect [60]); (2) the possibility of optimizing and refining the intervention over the course of the study based on the empirical data collected from the participants’ feedback [61]; and (3) the possibility of exploring heterogeneity between participants given that statistical inference can be produced at the individual level, which makes the tailoring of current and subsequent personalized interventions easier [62].

In recent years, some studies have been designed or implemented with the aim of promoting sustainable healthy eating behaviors [12,13]. However, to the best of our knowledge, this is the first study to address the overall dietary pattern, food waste, and socioeconomic dimensions of food in an intervention. In addition, the brief and continuous assessment implemented through the app will provide, for the first time in the domain of sustainable healthy diet, a high-resolution view of behavior changes useful for improving our understanding of the overall process compared with studies using traditional low-resolution measurement paradigms (eg, baseline and 3- and 6-month follow-ups). If we are able to manage potential technological issues that could happen with the app, the use of technology to monitor participants remotely should also help make this intervention minimally burdensome for the participants, as they do not need to attend in-person meetings.

### Conclusions

This study will address the urgent topic of adopting overall sustainable healthy diets, thus filling a gap in the literature and providing pilot data for scaling up the intervention in a full randomized controlled trial. It will provide insights into the effectiveness of the pilot intervention in changing eating behaviors toward a sustainable healthy diet, considering the whole dietary pattern and, hence, spillovers among food groups and among dietary outcomes; it will help to determine the moderation and interaction effects of several individual characteristics, such as socioeconomic level and gender; and it will address its own feasibility to determine the barriers to and enhancers of the intervention, which will help us refine and optimize the intervention for future studies.

## Appendix

Multimedia Appendix 1 Google form used for checking the inclusion and exclusion criteria (English and Spanish versions).

Multimedia Appendix 2 Scoring criteria for the dietary questionnaire included in the Google form to select participants.

Multimedia Appendix 3 Text messages (English and Spanish versions) to be sent to the participants during the intervention phase along with the behavior change techniques they match.

Multimedia Appendix 4 Baseline questionnaire (English and Spanish versions).

Multimedia Appendix 5 Supportive material showing specific food items gathered in the assessed food groups and examples of 1 and 0.5 servings (English and Spanish versions).

Multimedia Appendix 6 Interview guide (English and Spanish versions).

